## Abstract

**Background:**

In Nepal, the burden of noncommunicable, chronic diseases is rapidly rising, and disproportionately affecting low and middle-income countries. Integrated interventions are essential in strengthening primary care systems and addressing the burden of multiple comorbidities. A growing body of literature supports the involvement of frontline providers, namely mid-level practitioners and community health workers, in chronic care management. Important operational questions remain, however, around the digital, training, and supervisory structures to support the implementation of effective, affordable, and equitable chronic care management programs.

**Methods:**

A 12-month, population-level, type 2 hybrid effectiveness-implementation study will be conducted in rural Nepal to evaluate an integrated noncommunicable disease care management intervention within Nepal’s new municipal governance structure. The intervention will leverage the government’s planned roll-out of the World Health Organization’s Package of Essential Noncommunicable Disease Interventions (WHO-PEN) program in four municipalities in Nepal, with a study population of 80,000. The intervention will leverage both the WHO-PEN and its cardiovascular disease-specific technical guidelines (HEARTS), and will include three evidence-based components: noncommunicable disease care provision using mid-level practitioners and community health workers; digital clinical decision support tools to ensure delivery of evidence-based care; and training and digitally supported supervision of mid-level practitioners to provide motivational interviewing for modifiable risk factor optimization, with a focus on medication adherence, and tobacco and alcohol use. The study will evaluate effectiveness using a pre–post design with stepped implementation. The primary outcomes will be disease-specific, “at-goal” metrics of chronic care management; secondary outcomes will include alcohol and tobacco consumption levels.

**Discussion:**

This is the first population-level, hybrid effectiveness-implementation study of an integrated chronic care management intervention in Nepal. As low and middle-income countries plan for the Sustainable Development Goals and universal health coverage, the results of this pragmatic study will offer insights into policy and programmatic design for noncommunicable disease care management in the future.

**Trial registration:**

ClinicalTrials.gov, NCT04087369. Registered on 12 September 2019.

## Background

The burden of noncommunicable diseases (NCDs) is rising globally [1, 2], and four major NCD classes—cardiovascular disease, chronic respiratory disease, diabetes, and cancer—contribute to more deaths globally than all other diseases combined, with enormous health and economic implications currently and in the future [3, 4]. This is especially true in low and middle-income countries (LMICs), where governments are struggling to plan for the increasing health and financial implications of these pandemics [5]. As governments strive to achieve the Sustainable Development Goals [6] and work toward universal health coverage [7], the rising NCD pandemic poses significant barriers to these aspirations.

In spite of this growing need for long-term chronic disease care, LMIC healthcare systems are not well equipped to address this disease burden [8]. Historically focused on delivering acute, episodic care, these healthcare systems lack the capacity to provide ongoing longitudinal care for patients with diseases best managed across a lifetime. This is especially true for patients with multiple chronic conditions, who often struggle to receive care for comorbid diseases without numerous, fragmented encounters [9]. Health workforce shortages and an emphasis on physician-provided care have contributed to significant access, coverage, and quality deficits [10, 11].

There is a growing body of evidence that chronic diseases in LMICs can be well managed, especially at the primary care level, by mid-level practitioners (MLPs) [10, 12–21]. MLPs offer a feasible, affordable, and high-quality alternative to traditionally physician-delivered care. This can help to circumvent access barriers, thereby leading to fewer late-stage presentations and complications of otherwise manageable chronic conditions [20]. Evidence suggests that the quality of MLP-delivered care improved when they are well-managed, assigned clear scopes of work for which they are appropriately trained, and receive supportive supervision [22–24] from senior clinicians with continual, improvement-focused feedback [20].

Simultaneously, the role of community health workers (CHW) is increasingly recognized as an important augmentation to facility-based care delivery strategies, offering critical linkages, referrals, and coordination of care within communities [25–27]. The potential value of CHW-augmented chronic care management has only recently become of major interest [12–18, 27–29]. Global experience suggests that the greatest benefits come from CHWs when they are accredited, well-managed, salaried, continually trained and supervised, integrated into strong primary care systems, and part of continual data feedback loops with facility-based providers [25].

Taken together, the need and opportunity for LMIC healthcare systems—already struggling with workforce shortages—to build strong chronic care programs managed by MLPs and augmented with CHWs are compelling. However, there is a paucity of large-scale implementation data available to evaluate such models of care delivery, making it difficult for LMIC policy-makers to decide whether to adopt these strategies.

In response to the growing need for evidence-based NCD service delivery, the World Health Organization has compiled a set of protocols within the Package of Essential Noncommunicable Disease Interventions (WHO-PEN) for primary health care in low-resource settings [30, 31]. These protocols constitute simple decision-making algorithms for the screening, diagnosis, and management of major NCDs, helping to ensure quality care provision in primary care settings, especially in areas already struggling with workforce shortages.

The WHO, together with the World Heart Federation, the World Stroke Organization, the United States Centers for Disease Control, the International Society of Hypertension, and the World Hypertension League, has released complementary guidelines to the WHO-PEN, called HEARTS [32]. (The acronym stands for: Healthy-lifestyle counselling. Evidence-based treatment protocols. Access to essential medicines and technology. Risk-based charts. Team-based care. Systems for monitoring.) In addition to bringing specific guidelines for cardiovascular disease management into the technical base of WHO-PEN, these guidelines provide expanded details around health information systems, workforce development and training, and service delivery. As such, they augment the systems focus of WHO-PEN in incorporating NCD care into broader healthcare systems strengthening.

Recent evidence has shown the feasibility of adopting WHO-PEN at the primary care level in LMICs, including implementation with MLPs [33–36]. These data suggest that it is feasible to deploy WHO-PEN at the population level in primary care settings. While WHO-PEN and HEARTS do not focus explicitly on the engagement of CHWs in these care delivery chains, there is a strong potential for augmenting MLP-based WHO-PEN and HEARTS care at facilities with CHW-based strategies in the community.

Clinical decision support (CDS) tools facilitate the use of algorithmic care protocols such as WHO-PEN by health workers at the point of care. HEARTS provides specific CDS algorithms for cardiovascular conditions. These algorithmic CDS tools are used globally, across high-income and LMIC settings, in a range of conditions, including heart disease and diabetes [37–42]. CDS tools are essential both for managing individual conditions as well as for structuring the comprehensive care of patients with multiple comorbidities. In addition to CDS tools integrated into electronic health records (EHRs), there is a growing body of evidence to support mobile-phone-based CDS tools, often targeted at MLPs [43] and CHWs [44]. These CDS tools are especially well equipped for clinical situations in which clear algorithms exist, such as the WHO-PEN and HEARTS protocols.

Historically, in many LMICs, there has been scant emphasis placed on risk factor reduction through lifestyle modification for NCD prevention or to reduce risk factors for the progression of these diseases when already diagnosed. While many of the contributing etiologies for NCD epidemics are far upstream of individuals’ lives, and out of their control [45], there are certain risk factors that are modifiable by patients, families, and health workers. Among others, it is widely documented that alcohol and tobacco consumption directly contribute to the development and progression of cardiovascular disease, diabetes, and chronic obstructive pulmonary disease (COPD) [46]. These risk factors have been marked as priority targets for NCD control moving forward, including in both the WHO-PEN and HEARTS protocols [8, 47].

WHO-PEN Protocol #2 (republished in HEARTS), “*Health Education and Counseling on Healthy Behaviors*,” describes risk factor modification [31]. However, while emphasizing health education, there is often very little guidance provided to health workers for meaningful engagement with patients and communities to accomplish these difficult lifestyle modification goals. There are many limitations to purely knowledge-focused approach health education, versus one that emphasizes self-efficacy and patients’ own values [48].

Motivational interviewing (MI), originally validated in substance-abuse interventions, approaches behavior change through a style characterized by empathy and collaboration aimed toward the patient’s readiness for change [49]. Trial data demonstrate the efficacy of MI for behavior change such as smoking and alcohol cessation [50–55]. These data raise the possibility of MI program development, led by MLPs within LMICs, as a viable strategy for improving risk factor modification interventions, and, specifically, as an augmentation to WHO-PEN, to strengthen its impact. Since many communities struggle with a lack of healthy nutritional options, dietary improvements are often difficult to realize. Reducing alcohol and tobacco consumption, however, are realistic options for risk factor modification interventions in even the poorest communities worldwide. Recent WHO-PEN guidance on “brief interventions” for alcohol and tobacco, in concert with MI-related interventions, offer practical options for addressing these challenges in the primary care setting [48].

In Nepal, the burden of NCDs is rapidly growing [56–58], within the context of an overburdened healthcare system [12, 58, 59]. Nepal’s government is committed to achieving the Sustainable Development Goals and universal healthcare, and has a specific focus on expanding health services for NCDs. In addition to recently enshrining the right to healthcare into its Constitution [60], Nepal’s government has committed to addressing the NCD epidemic by launching a Multisectoral Action Plan in 2014 [61] and establishing the Nepal Noncommunicable Disease & Injury Poverty Commission in 2016 [58]. Furthermore, the Ministry of Health and Population has committed to a step-wise national implementation of PEN [58, 59, 62]. Nonetheless, the way forward will be challenging, and innovative strategies are clearly needed to accomplish these ambitious goals [58].

Nepal has an extensive history of both MLP and CHW interventions [63–65]. Recent evidence from within the country has demonstrated the potential for CHWs to be involved in hypertension management [66]. Many communities rely on MLPs for primary care [43, 67], and there has been some experience with MLPs using CDS tools for algorithmic care provision [43]. However, to date there are no large-scale implementation data for integrated, MLP-based and CHW-based NCD care management at the population level. Similarly, while there has been some anecdotal description of MI being utilized in urban areas for select populations, there is no population-level data surrounding the use of MI for NCD risk modification. As the country endeavors to develop cross-sectoral strategies to address the growing NCD epidemic, these staffing models, coupled with CDS tools and MI-based adherence and risk modification, are important policy and programmatic considerations.

We will conduct a type 2 hybrid effectiveness-implementation trial (where effectiveness and implementation are simultaneously tested with equal priority simultaneously) [68, 69] to evaluate an integrated NCD care management intervention. The intervention will leverage the Nepali government’s planned roll-out of WHO-PEN in two rural districts. In addition to the government’s roll-out, the intervention will include three evidence-based components: NCD care provision by MLPs and CHWs that is integrated between facilities and communities; CDS tools for MLPs and CHWs to optimize adherence to best practices; and training and supervision of MLPs in using MI to facilitate tobacco and alcohol cessation.

## Methods

### Study aims

As already stated, we will conduct a type 2 hybrid effectiveness-implementation trial to evaluate an integrated NCD care management intervention in rural Nepal. The intervention is described in depth in Additional file 1.

### Study implementers

Healthcare workers and research staff from the nonprofit organization Nyaya Health Nepal, their collaborators in the Ministry of Health and Population and Nepal Health Research Council, and collaborating researchers form the study team will lead the study. Nyaya Health Nepal has been working in a public–private partnership with the Ministry of Health and Population for over 10 years in rural Nepal to deliver community-based and facility-based health services, and this study will leverage this pre-existing partnership and care delivery network. Nyaya Health Nepal operates with a US-based nonprofit organization, Possible, to advance national and global healthcare systems policy and practice priorities.

### Study setting

The study will take place in the Achham and Dolakha districts of Nepal across four municipalities. Following recent healthcare decentralization, Nepal’s 750 municipalities manage primary healthcare delivery. The intervention will be implemented in a step-wise fashion in coordination with municipal-level government authorities and study staff.

Achham is a remote, impoverished district of 260,000 people, with large migrant populations and a history of social disruption during the Nepali civil conflict [70–74]. Achham has one of the highest district-level under-5 mortality rates [75] and one of the lowest human development indices in the country [76]. The study implementers have been delivering some NCD-related care at the district-level Bayalpata Hospital and to communities within the hospital’s catchment population since 2008. Bayalpata Hospital serves approximately 90,000 outpatient and 3000 inpatient visits per year. CHW services include proactive case detection, care coordination, and counseling. The study will include a catchment population of approximately 50,000 in Achham across two municipalities.

The second district is Dolakha, one of the hardest hit districts in the 2015 earthquakes [77]. Nyaya Health Nepal’s work in Dolakha is based at Charikot Primary Health Care Center, which serves approximately 60,000 outpatients per year, with similar CHW services to those in Achham’s. The study will include a population of approximately 30,000 in Dolakha across two municipalities. Thus, the total expected study population will be 80,000.

Within the context of the public–private partnership between the government and Nyaya Health Nepal, no user fees are charged for any facility-based or community-based services, in either Achham or Dolakha, thereby mitigating financial access barriers to care delivery and study participation.

Within the study setting, MLPs for the NCD intervention are locally defined as the Nepali cadre of health assistants, who have 3 years of postsecondary medical training. The CHWs in this intervention have secondary-school-level education and are fully employed, with ongoing supervision from community health nurses (CHNs). They receive initial training of approximately 1 month when they are hired, and ongoing weekly trainings to continually improve their skillsets. The CHWs are employed by the public–private partnership between Nyaya Health Nepal and the Ministry of Health and Population. They are distinct from the robust Female Community Health Volunteer network that exists throughout Nepal [63, 78], who have historically focused on vaccination, public health messaging, and other community preventive interventions rather than on household care delivery and follow-up. These staffing, supervision, and training structures are described in greater detail in Additional files 1 and 2.

### Study populations

For primary quantitative outcomes, the study population will include adult patients (≥ 18 years of age) who qualify for a diagnosis of hypertension, type II diabetes, and/or COPD, according to WHO-PEN guidelines, and are engaged in longitudinal care by Nyaya Health Nepal’s team in Achham and Dolakha. The study will limit enrollment to the catchment areas served by both the facility-level and CHW-level services deployed by Nyaya Health Nepal. Study participants will be initially enrolled during facility-based visits at Bayalpata Hospital and Charikot Primary Health Care Center prior to the completion of intervention roll-out, and are considered engaged in longitudinal care if they have at least one follow-up hospital visit after 12 months of their initial visit. Digital health records that link between the facility-based EHR and the CHWs’ mobile-phone applications will be utilized to share patient data across settings, when available. CHWs can identify potential patients in the community and refer them to the facility for diagnosis confirmation, following which they could be included in the study. Patients’ receipt of care will not be contingent upon their enrollment in the study; all patients will continue to receive care per routine service delivery. This represents an exhaustive convenience sampling method as all eligible patients identified at Bayalpata Hospital and Charikot Primary Health Care Center may be enrolled in the study. Exclusion criteria are individuals planning to migrate from the study area prior to 12 months of exposure to the intervention, or individuals explicitly requesting exclusion from the study or declining to consent (see Additional file 3) for the study.

For implementation components, staff members, patients, community leaders, and government officials will be approached for key-informant interviews (KIIs) and focus group discussions (FGDs), as described in the following.

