### Study outcomes

The study has two specific aims: effectiveness (Specific Aim 1) and implementation (Specific Aim 2), as detailed in Table 1. For Specific Aim 1, the primary outcome will be the proportion of patients who meet disease-specific, evidence-based control measures at the completion of their initial 12 months engaged in treatment. These “at-goal” metrics aim to serve as simplified measures to assess disease control status, recognizing the limitations associated with multiple disease-specific metrics in settings like rural Nepal, especially for patients with multiple comorbid conditions. These are presented in Table 2.

**Table 1 Tab1:** Metrics for Specific Aim 1 (efficacy) and Specific Aim 2 (implementation)

Aim	Outcome/RE-AIM element	Indicator	Definition
Specific Aim 1: efficacy	Primary outcome: control of NCD conditions	Condition-specific “at-goal” metrics	% of enrolled NCD patients achieving “at-goal” status (Table 2), at completion of the study period
	Secondary outcome 1: tobacco use	Tobacco use status	% of enrolled NCD patients who were using tobacco at enrollment who are nonusers or who have reduced by > 50% their tobacco intake, at completion of the study period
	Secondary outcome 2: alcohol use	Alcohol use status	% of enrolled NCD patients who were alcohol drinkers at enrollment who are nondrinkers or who have reduced by > 50% alcohol intake, at completion of the study period
Specific Aim 2: implementation	Reach	Home visit coverage	% of enrolled NCD patients having a CHW home visit, measured monthly
		Clinic visit coverage	% of enrolled NCD patients having an MLP visit at the clinic, measured monthly according to the patients indicated to be seen that month based on protocol-based guidelines
		Demographic, geographic barriers and facilitators	% of enrolled NCD patients whose CHW has GPS-mapped their households, describing barriers/facilitators to individuals’ access, and identifying contributors to variation/inequities
		Loss to follow-up	% of patients, stratified by demographic data and NCD conditions, who are lost to follow-up after enrollment
		Monthly patient touch-points	Number of monthly per-patient touch-points, including interactions by both MLPs and CHWs
	Efficacy	Evidence-based hypertension management	% of enrolled hypertension patients in accordance with evidence-based recommendations, as prescribed by clinical algorithms, assessed quarterly by EHR audits

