### Sampling strategy and power calculations

We will use exhaustive convenience sampling to screen all eligible patients seen across two facilities over a 12-month period into the analysis cohort. Based on historical formative data of patient volume seen at these two facilities, and accounting for an expected 30% attrition rate, we conservatively expect that at least 1000 patients will be eligible for enrollment into the cohort.

With this conservative number of 1000 as our expected sample size based on this convenience sampling, we conducted power calculations to determine the statistical power to detect a change in the “at-goal” status. We calculate power based on a simplified design to compare paired proportions using a two-sided McNemar’s test with an 0.05 type I error (α) level. The primary outcome is the proportion of patients who achieve their NCD control target (“at-goal status”) after 12 months of being engaged in care. We used SAS version 9.4 (Cary, NC, USA) to estimate power to detect a 5% difference between discordant proportions; that is, proportions of patients whose “at-goal” status changed from “not at-goal” at baseline to “at-goal” at follow-up, and vice versa, in multiple scenarios where the total proportion of discordant patients ranged from 10 to 40% of all patients. Based on these assumptions, our power to detect a 5% difference in the discordant pairs is 69%, when the total discordant proportion is 40%, and the power is 99% when 10% of all patients are discordant.

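### The primary-outcome population is restricted to patients who return after month 12, so the pre-post gain is conditioned on retention and does not match the enrolled-patient denominator in Table 1

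*Protocol article*

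**What the plan says.** Four places in the protocol article bear on who is counted.

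- **Study populations.** For the primary quantitative outcomes, patients must have a qualifying diagnosis "and are engaged in longitudinal care by Nyaya Health Nepal" staff. Patients "are considered engaged in longitudinal care if they have at least one follow-up hospital visit after 12 months of their initial visit". The same section says that participants are first enrolled at a facility visit, so enrolment and engagement are two separate states.
- **Sampling strategy and power calculations.** The cohort size is already net of dropout: "accounting for an expected 30% attrition rate, we conservatively expect that at least 1000 patients will be eligible for enrollment into the cohort". Power is then computed "With this conservative number of 1000 as our expected sample size based on this convenience sampling", all treated as complete pairs.
- **Study outcomes, Table 1.** The primary indicator is the percentage of enrolled NCD patients at goal when the study period ends. Under Reach, loss to follow-up is the percentage "of patients, stratified by demographic data and NCD conditions, who are lost to follow-up after enrollment".
- **Study design and Analysis for Specific Aim 1.** The design is pre-post without a control group. The primary analysis is a conditional logistic regression at 12 months, and the hypothesis is a 10% increase in at-goal status.

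**The concern.** Under the Study populations rule, nobody's membership of the primary cohort is known until after month 12. A patient who dies, stops attending or is last seen at month 11 is not a participant with a missing outcome. That patient is outside the population altogether. A later analysis plan could not repair this by imputation, because the excluded patients are not in the set to be imputed.

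This matters for two reasons. The programme aims to keep patients in care, and the study is meant to inform population-level policy, yet success would be scored only among those who stayed. And because there is no comparison group, nothing offsets a link between returning and improving.

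The denominator is also unsettled. Table 1 counts enrolled patients and Study populations counts engaged patients. The sampling section then uses the language of enrolment for a number from which attrition has already been deducted.

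**Working it through.** **1. The plan's own figure.** Inputs from the sampling section: N = 1000, a test to "compare paired proportions using a two-sided" McNemar procedure at alpha 0.05, a 5-point difference between the discordant proportions, and 10% to 40% of patients discordant. The exact McNemar power is 69.0% at 40% discordant and 99.9% at 10% discordant. The plan states 69% and 99%. The power arithmetic is sound; the problem is who the 1000 are.

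**2. How many are left out.** The 30% attrition is read here as failure to return after 12 months, which the article does not spell out.

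- Starters: 1000 / (1 - 0.30) = 1,429 (rounded).
- Outside the primary population: 1,429 - 1000 = 429.

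**3. Gain in all starters.** The article gives neither outcomes for leavers nor a baseline at-goal rate, so only a range under assumptions can be shown. The hypothesised 10% is read as 10 percentage points and assigned to the patients who stay.

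Gain in all starters = 0.7 x (gain in stayers) + 0.3 x (change in leavers)

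| Assumed change in leavers | Calculation | Gain in all starters |
|---|---|---|
| +10 points | 0.7 x 10 + 0.3 x 10 | +10 |
| none | 0.7 x 10 + 0 | +7 |
| -10 points | 0.7 x 10 - 0.3 x 10 | +4 |
| -20 points | 0.7 x 10 - 0.3 x 20 | +1 |

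The gain reaches zero when leavers lose 7 / 0.3 = 23.3 points, which is possible only if at least 23.3% of them were at goal at baseline.

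**4. Leavers counted as not at goal.** Assume the same baseline at-goal rate p0 in stayers and leavers.

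Gain in all starters = 0.7 x (p0 + 10) - p0

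- p0 = 10%: 0.7 x 20 - 10 = +4
- p0 = 20%: 0.7 x 30 - 20 = +1
- p0 = 30%: 0.7 x 40 - 30 = -2

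**5. Does another section bring the leavers back?** The regression adjusts for the number of encounters, but that adjustment operates only among patients already in the population. The Reach metric can make attrition visible, but it does not change the primary estimate. Table 1's enrolled denominator would include the leavers, but it conflicts with the population defined in Study populations, and the article does not say which governs.

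**The case against.** The strongest reply is that the protocol states its target openly, namely control after 12 months in care, and that it reports loss to follow-up separately. A retained-patient result can be interpreted if it is labelled as such. The comparison is paired within patients, so a difference in baseline control between stayers and leavers does not by itself create a gain. Some loss may be relocation in districts with much migration rather than failure of control. The choice of imputation or weighting is commonly left to an analysis plan that is not shown.

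Most of this stands, and it rules out three stronger readings that a reader might infer.

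- *Loss to follow-up in Table 1 must be zero by construction, and visit coverage is inflated.* The documents do not support this. Study populations separates initial enrolment from engagement and ties the engagement rule to the primary outcomes, while the Reach metrics are defined on enrolled patients. Loss can therefore be about 30%.
- *Selection could manufacture the whole hypothesised gain.* The arithmetic does not show this. It takes a 10-point gain in stayers as given and dilutes it. The result falls below zero only when every leaver counts as not at goal at an assumed baseline such as 30%, or when leavers lose more than 23.3 points.
- *The bias is known to favour the intervention.* Overstatement is likely, because patients who stay tend to be better controlled, but the article has no data on leavers.

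The objection does not remove the selection itself. The rule is stated text, not omitted detail, and pairing does not protect against a link between returning and the change in control.

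**Conclusion.** The point holds in this form: the primary pre-post estimate is conditioned on a post-baseline visit, about 429 of about 1,429 starters are left out, and the rule conflicts with the enrolled denominator of the primary indicator in Table 1. Without a control group, selective retention cannot be told apart from an effect of the intervention.

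The size depends on assumptions that the article does not settle. If leavers improve as much as stayers, there is no bias. A 10-point gain in stayers is +7 in all starters with leavers unchanged, +4 if they lose 10 points, and between +4 and -2 if leavers count as not at goal at baselines of 10% to 30%. These figures rest on the plan's 30% attrition, on reading the 10% hypothesis as percentage points and, for the last range, on equal baseline rates in stayers and leavers.

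**What to change.** - Remove the visit after month 12 from the definition of the primary population.
- Define the cohort at the initial visit as all consenting eligible patients with a baseline status, so that it matches the enrolled denominator of the Table 1 primary indicator.
- Handle missing month-12 status by multiple imputation or inverse-probability weighting on baseline data, with a sensitivity analysis that counts lost patients as not at goal.
- Report the retained-only result as secondary, and label it as such.
- State that the Table 1 Reach and loss-to-follow-up metrics use the same all-enrolled denominator.
- In the sampling section, give the number enrolled and the number expected with a month-12 status separately: at 30% attrition, 1000 observed pairs correspond to about 1,429 enrolled.

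The cost is revised wording and modest extra analysis. There will be more missing data to model, and the estimate will probably be smaller and less precise.
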